## Methods

### Overview of the study design

The study population is divided into two groups: the intervention group (which performs individual interventions for drinking habits, including the results and points to note concerning genotypes determined using saliva) and the control group (which has no constitutional examination during the study period, providing only conventional teaching materials). This study is an open-label, randomized controlled trial. We chose an open-label trial because participants can be distinguished between the intervention group, who undergoes the test of genotypes at baseline, and the control group, who wishes to test for genotype after 6 months of study. In principle, the outcome evaluator does not provide interventional care, and only the outcome evaluator is blinded.

Figure 1 shows the study flow chart, and Table 1 lists the components of the five genotypes of alcohol-metabolizing enzymes and the major health risks.

**Fig. 1 Fig1:**
[figure not shown]
Study flow chart. *ALDH2* aldehyde dehydrogenase 2, *ADH1B* alcohol dehydrogenase 1B

**Table 1 Tab1:** Composition of five genotypes of alcohol-metabolizing enzymes and the health risks (supervised by National Hospital Organization Kurihama Medical Center. Partial excerpt) [1]

Aldehyde dehydrogenase	Alcohol dehydrogenase	Type classification of this research	Comments on constitution and health risks
*ALDH2 *1/ *1* (activity)	*ADH1B *1/ *1* (low activity)	A (3%)	The highest risk of alcohol addiction
	*ADH1B *1/ *2* (activity)	B (50%)	Decomposition of alcohol and acetaldehyde is fast. Be careful not to drink too much for your health.
	*ADH1B *2/ *2* (high activity)		
*ALDH2 *1/ *2* (low activity)	*ADH1B *1/ *1*	C (3%)	The decomposition of alcohol and acetaldehyde is slow, and the cancer risk is high, owing to acetaldehyde.
	*ADH1B *1/ *2*	D (40%)	Face turns reddish immediately. Nausea and other discomfort can occur. Symptoms and health problems are likely to occur.
	*ADH1B *2/ *2*		
*ALDH2 *2/ *2* (Inactive)	*ADH1B *1/ *1*	E (4%)	Drinking is intolerable because aldehyde cannot be decomposed. Very small amounts of alcohol are prone to unpleasant symptoms such as hot flushes, drowsiness, palpitation, and nausea. Even a small amount of alcohol is at risk of acute alcohol intoxication.
	*ADH1B *1/*2*		
	*ADH1B *2/ *2*		

### Study setting

This study is being conducted at a national university in the metropolitan area in Japan and is recruiting participants. The university is a comprehensive university, including medical departments. In 2021, the total number of students and faculty members were 16,542 and 4,608, respectively.

### Participants

We included students and graduate students, and staff aged 20–30 years at the University of Tsukuba. The average amount of daily or one-occasional drinking is more than 40 g of pure alcohol for males and more than 20 g for females. They provided their consent to participate in this research.

The exclusion criteria are those who did not wish to disclose the results of the alcohol constitution test and those who have difficulty communicating in Japanese. Participation is voluntary, and participants will be withdrawn if they request to stop participating.

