**Methods:**

Participants comprised university students and staff aged 20–30 years who had consumed ≥40 g (males) or ≥20 g (females) of pure alcohol; they were classified into intervention and control groups using a simple randomization method. Participants anonymously filled out questionnaires linked to identification numbers and recorded the drinking days and amounts on the drinking calendar. The intervention group will then be tested for genotype testing using saliva (5 types of combinations of *ALDH2* and *ADH1B* enzyme activities); the result report will arrive approximately 1 month later. We will conduct a 30-min face-to-face or online intervention. The control group will be merely given the conventional materials, and genetic testing will be performed voluntarily after 6 months (end of study). The intervention group will undergo questionnaire surveys 1 month after the intervention and 3 and 6 months after baseline. Questionnaire surveys will be conducted 1, 3, and 6 months after baseline for the control group. The average amount of drinking before and after the intervention, attribute/baseline data between the two groups, and time-series data were compared using various analysis tools. For interventions, we engaged in dialog based on intervention materials that added genotyping content to the existing materials, result reports, baseline data, and drinking calendar records. Participants’ ingenuity is respected to support their drinking behavior and goal setting.

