### Screening and informed consent

Simultaneously, as the consent procedure, a self-administered questionnaire survey of baseline data are conducted, and the explainer confirmed the drinking status and average drinking amount during questionnaire collection. The procedure for explanation and consent is mainly conducted by the first author. With written consent, the intervention group is tested for alcohol-metabolizing enzyme genotype using saliva. The explainer collect and mail the sample to the testing institution on the day of the test. On the consent form, participants will be asked if they agree to the use of their data, should they choose to withdraw from the trial. Participants will also be asked for permission by the research team to share relevant data with people from the universities participating in the study or, if necessary, from regulatory agencies. If the consent and permission are confirmed, the data can be used and shared. This study does not include collecting biological specimens for storage.

During the time of study planning and implementation, measures against coronavirus disease 2019 (COVID-19) are required. Informed consent is supposedly obtained in person; however, depending on the participant’s wishes and place of residence (during homecoming, etc.), explanation, consent, and inspection procedures are performed online and by mail, as necessary.

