### Randomization

In randomization, we simply used a computer-generated random number table, collate participants with anonymizing identification numbers, and assign them to the intervention group or the control group (100 participants per group). The first author mainly marked the random number table as the identification number of the intervention group before the start of recruitment and assigned it in the order of registration depending on the presence or absence of the mark.

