### Statistical analysis

Baseline data and participant attributes, average drinking amount on drinking days, AUDIT-C and AUDIT scores, and response at each scale of secondary outcome measures at each measurement point will be analyzed by a descriptive statistic.

Furthermore, baseline data, attributes, and changes in the average daily drinking amount (1 drink = 10 g of pure alcohol) before and after intervention are compared with the differences between the two groups. We will also compare the measurement points within the groups and compare the groups in terms of genotypes. For these analyses, we use the *t*-test, paired *t*-test, Wilcoxon rank-sum, chi-square, Mann–Whitney *U*, and Kruskal–Wallis tests as appropriate. The selection of the analysis method depends on the parametric and nonparametric data obtained from the results of descriptive statistics and normality tests to determine. In addition, the change in the average amount of drinking (1 drink = pure alcohol 10 g) in each group is examined by calculating the effect size. Data will be analyzed using IBM SPSS Statistics for Windows version 28. If the intervention is not possible in the intervention group, or if no response will be obtained after 1 month in the control group, it will be excluded from the analysis.

Regarding qualitative data (positive aspects about the alcohol constitution test, reasons, etc.), we will examine them by using an inductive analysis method with qualitative coding. The code extracted to ensure reliability will be analyzed by multiple researchers, including those with qualitative research experience.

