## Alcohol-metabolizing enzyme genotype testing and results report

Briefly, the intervention group will read the instructions for the alcohol-metabolizing enzyme test, sign the consent form, undergo saliva collection using a sponge swab from the test kit, and receive a report of the results approximately after 1 month. The inspection contractor will mail the result report to the participants. If face-to-face explanation and inspection are difficult to conduct, the test kit will be mailed to the participants.

In the control group, testing will be conducted on those who wish to be tested after 6 months from baseline. After receiving the test results, their requests will be confirmed, and the intervention will be performed.

Regarding the report of the results of the alcohol-metabolizing enzyme test, we have created a pamphlet that includes contents common to each of the five types of constitutions and the contents for each constitution. The main contents are as follows:Participants’ alcohol constitution (what type of constitution from A to E, characteristics by constitution type)Mechanism of alcohol decomposition, function of metabolic enzymes, and constitution by combinationRisks of diseases associated with drinking by alcohol constitution (every five types) and points to remember (comments by the constitution)How to interact with and drink alcohol that suits participants’ alcohol constitution, and how to absorb alcohol ingenuity in nutrition and eating and drinking to help slow down the metabolismDrinking habit screening test (AUDIT-C)Appropriate drinking and liver rest days, proper drinking method, alcohol calorie, and metabolism, obesity, etc.Inappropriate drinking: drinking while pregnant/lactating, drunk driving, alcohol harassment, and habitual use/heavy drinking

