As mentioned in the introduction, a randomized controlled trial using the genetic information of the alcohol-metabolizing enzyme *ALDH2* validated the effect 30 days after providing Internet-based *ALDH2* genotype and health risk information [13]. In this previous study, the frequency and amount of drinking were significantly reduced after 30 days in the feedback group with low *ALDH2* activity. However, their follow-up period was 30 days, which is shorter than 6 months (maintenance period) [28], for behavioral habituation and maintenance. Therefore, the strength of the current study is the investigation of the intervention effect until 6 months (maintenance period) [28], which is the standard duration for behavioral habituation, and verification of its long-term efficacy.

Conversely, one limitation of this study is that when students agree to participate, they already know if they are in the group to be tested or not; hence, they cannot be blinded. Regarding the primary outcome measure, the average drinking amount on the drinking day is limited to the calculation of the amount of drink with an unknown alcohol concentration or amount. In addition, given that this research deals with genetic information, we need to evaluate the intervention effect by interviewing each participant. We also need to examine a system that can be useful for enrolling large groups, such as university students.

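### The exclusion of people who do not want their test result disclosed can act unequally between arms, because allocation is known at consent and control testing is optional

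*Protocol article*

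**What the plan says.** All references are to the protocol article.

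- **Participants:** "The exclusion criteria are those who did not wish to disclose the results of the alcohol constitution test", together with people who have difficulty communicating in Japanese. The rule is written for everyone, with no arm and no time point.
- **Randomization:** the first author mainly marked a random number table before recruitment and "assigned it in the order of registration depending on the presence or absence of the mark".
- **Screening and informed consent:** "The procedure for explanation and consent is mainly conducted by the first author". The baseline questionnaire is completed at the same time. Testing follows in one arm: "With written consent, the intervention group is tested for alcohol-metabolizing enzyme genotype using saliva".
- **Alcohol-metabolizing enzyme genotype testing and results report:** "In the control group, testing will be conducted on those who wish to be tested after 6 months from baseline". The abstract also describes control testing as voluntary and at the end of the study.
- **Discussion:** the limitation is stated that "when students agree to participate, they already know if they are in the group to be tested or not". It is presented as a lack of blinding and not as a matter of who enters each arm.

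**The concern.** Take a student who would rather not learn, or not share, a genotype result. If that student is told they are in the tested group, they must decline or be excluded. If told they are in the control group, they can complete all 6 months of follow-up without being tested. The allocation list may be random and the two groups still differ in who stayed.

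Willingness to receive a personal alcohol risk is plausibly linked to readiness to change drinking. The trial itself measures stage of change as a secondary outcome. If the intervention arm is left with the more willing people, the comparison of drinking amounts mixes the effect of the intervention with the effect of selection. An open-label trial does not need to accept this, because allocation can be revealed after consent and baseline. The Background describes a 2006 workplace study in which employees who already wanted their result were then randomised, so willingness was settled for both groups beforehand.

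Two other rules could hide the loss. Statistical analysis drops people by a different condition in each arm: "If the intervention is not possible in the intervention group, or if no response will be obtained after 1 month in the control group". Monitoring stops recruitment once the number to be analysed reaches target, so the final counts could look balanced after unequal losses.

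**Working it through.** **Step 1. Does the text allow unequal action?**

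| Question | Intervention arm | Control arm |
|---|---|---|
| Group known when agreeing to take part? | Yes (Discussion) | Yes (Discussion) |
| Test carried out when? | At the consent stage | After 6 months |
| Test needed to remain in the arm? | Yes, the intervention uses the result | No, testing is for those who wish it |
| Stated check of willingness before allocation is revealed? | None stated | None stated |

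Reluctance bites at entry in one arm and need never come up in the other. The text neither prevents this nor says that it happens.

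**Step 2. The plan's own benchmark.** Sample size gives a total of 199 for a size of 0.2, α 0.05 and power 0.8, without naming the metric.

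- Paired t-test, d = 0.2, two-sided: n = 198.15, rounded up to 199. This matches exactly.
- Two-group ANOVA, f = 0.2 (equal to d = 0.4): 198.16 in total, or 200 with equal arms. This is close.
- Independent t-test, d = 0.2, two-sided: 393.4, so 394 per arm and 788 in total. This does not match.

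The 0.2 therefore cannot safely be read as a between-group difference of 0.2 SD, and shares of both 0.2 and 0.4 SD are shown below.

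**Step 3. Size of the bias if reluctant people are lost from the intervention arm alone.** Let r be the share who would refuse, and D the difference in mean outcome between refusers and willing people, in SD units. Both are assumptions. With no intervention effect:

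- intervention mean = W, the mean among willing people
- control mean = (1 − r) × W + r × (W + D) = W + r × D
- spurious difference b = r × D

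With 100 per arm, SE = √(2/100) = 0.1414 SD. Two-sided type I error = Φ(b/SE − 1.96) + Φ(−b/SE − 1.96). For example, r = 10% and D = 0.5 give b = 0.05 and b/SE = 0.354, so type I error = Φ(−1.606) + Φ(−2.314) = 0.064.

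| r | b for D = 0.2 / 0.5 / 0.8 (SD) | Type I error | Share of 0.2 SD | Share of 0.4 SD |
|---|---|---|---|---|
| 2% | 0.004 / 0.010 / 0.016 | 0.050 / 0.051 / 0.052 | 2–8% | 1–4% |
| 5% | 0.010 / 0.025 / 0.040 | 0.051 / 0.054 / 0.059 | 5–20% | 2.5–10% |
| 10% | 0.020 / 0.050 / 0.080 | 0.052 / 0.064 / 0.087 | 10–40% | 5–20% |
| 20% | 0.040 / 0.100 / 0.160 | 0.059 / 0.109 / 0.205 | 20–80% | 10–40% |

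These are upper limits for each r and D, because any reluctant control who is also excluded reduces the bias. If everyone's willingness is settled before allocation is revealed, b from this source is 0 for any r and D.

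**The case against.** A reader might infer that the criterion removes people from the intervention arm only. The document does not say so. The exclusion is a single rule for all participants. A control candidate who voiced reluctance could be excluded under it as well, and the design overview loosely describes controls as people who wish to be tested after 6 months. Optional uptake later does not show that the entry rule was waived. This objection stands, and the point is limited to a rule that can act unequally.

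The order of steps is also only partly visible. The flow chart is not shown, the article condenses a full protocol, and eligibility might be settled before registration. That is possible. However, the text that is shown places knowledge of the group at or before agreement and never places the willingness question ahead of it.

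The word *disclose* may mean learning the result or sharing it with researchers. The link to readiness to change is stronger on the first reading. On either reading the rule bites first in the arm that is tested at entry.

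It can be said that the root problem is known allocation, since someone told they will be tested could decline even without the criterion. That is right, and it is why the remedy changes the order of steps and leaves the criterion in place.

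Finally, people who answer a recruitment poster may seldom refuse, and no input to the size calculation comes from the document. That stands too, so no single figure for the bias is claimed.

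**Conclusion.** The concern holds in a limited form. As described, the exclusion can remove reluctant people unequally, because allocation is known at consent, testing is immediate in one arm and optional after 6 months in the other, and nothing fixes that willingness is asked of everyone beforehand. That it acts on the intervention arm alone is not established.

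The size is unknown. Under one-arm loss with 100 analysed per arm, about 2% refusal leaves type I error at 0.050–0.052, which is negligible. At 10% refusal the bias is 0.02–0.08 SD, with type I error of 0.052–0.087. At 20% the error can reach 0.205. These results rest on assumed refusal shares and on assumed differences of 0.2–0.8 SD. The direction depends on the sign of D: the bias favours the intervention if reluctant people would have reduced their drinking less. The change is worth making because it removes this source of bias for later entrants whatever the true values are.

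**What to change.** For all remaining entrants:

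1. Ask every candidate whether they agree to be tested and told the result, either now or after 6 months, and record the answer.
2. Take written consent and collect baseline data.
3. Apply the exclusion at that point, identically for everyone.
4. Only then reveal the allocation. Until then, keep the marked list from the person taking consent.

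For those already enrolled, report refusals and exclusions by arm, with the stage at which each occurred. Any sensitivity analysis should use willingness stated at consent, where it was recorded. Uptake of testing by controls after 6 months should not be used, because that choice follows the outcome and may depend on it.

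The cost is one consent question, a reordering of steps, and a protocol amendment that needs review-board approval under the Ethics and dissemination section. The consent procedure would also differ before and after the change, which must be reported. No extra participants or tests are needed. The benefit is confined to people enrolled after the change, and the article describes recruitment as still open.

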### Sample size

With reference to previous studies [13, 22], the total sample size was 199, calculated with a power size of 0.2, an *α* error of 0.05, and a power of 0.8 using the power analysis software (G * Power3) [24]. In total, we include 200 participants (100 in the intervention group and 100 in the control group).

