One of the effective intervention methods presented by the National Institute on Alcohol Abuse and Alcoholism for overdrinking among college students is a simple method known as Brief Alcohol Screening and Intervention for College Students (BASICS). BASICS includes initial screening to identify high-risk drinkers, subsequent baseline assessments to generate individualized feedback, and one-on-one meetings with trained facilitators to confirm feedback [21]. According to a 2020 report of a randomized clinical trial conducted in India by Kumar et al. [22], out of 793 students from two universities screened using the Alcohol Use Disorder Identification Test (AUDIT), 130 had an AUDIT score of 8–19. These 130 participants were randomly assigned to two groups: an experimental group (*n* = 64) with individually tailored brief intervention by trained nurses and a control group (*n* = 66), which only received general advice. Intervention effectiveness was assessed 3 months after one session of screening and brief intervention (SBI) and compared in terms of the changes in the AUDIT score and the percentage of students transitioning from the high-risk zone to the low-risk zone between the two groups. According to the results, SBI provided by individual-based nurses reduced the severity of problems or hazardous drinking in the short term (after 3 months of intervention), but the estimated effect size was small (0.16) [22]. In addition, face-to-face individual interventions are costly and difficult to disseminate on a large scale; thus, the effectiveness of individual short-term alcohol interventions provided by computers for heavy-drinking college students and young adults has also been tested. In a 2015 US review, the effects of computer delivery interventions were positive but small [23].

Integrating the results of previous studies above, interventions for excessive drinking in college students and young adults will be more effective and enduring with individual brief interventions using gene polymorphism information for alcohol metabolism than previous brief interventions. Moreover, this intervention may enhance the effect of correcting excessive drinking, especially in Japan, where *ALDH2* is often inactive. This randomized controlled trial aims to clarify that.

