## Monitoring

Although this study is an intervention study, it is an educational intervention, and saliva testing is not considered invasive. Therefore, there is no data monitoring. To maintain compliance, we collaborate with researchers to attend monthly online meetings to share progress, data collection, and intermediate analysis results and discuss issues. Regarding the decision to suspend the recruitment of participants, the progress of the trial will be shared at the meeting, and if there is no problem in conducting the exam, the recruitment will be suspended when the number of subjects to be analyzed reaches the target. This research is subject to progress checks and audits every 6 months by the Institutional Review Board, and the person in charge of the audit is independent of this study.

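### The sample size of 199 names neither the test nor the effect-size metric; if 0.2 means a standardised difference between arms, 100 per arm gives about 29% power, not 80%

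*Protocol article*

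**What the plan says.** In the Protocol article, Methods, Sample size, the authors refer to two earlier studies and report that "the total sample size was 199, calculated with a power size of 0.2", an alpha of 0.05 and "a power of 0.8 using the power analysis software". The total is then rounded up and divided: "100 in the intervention group and 100 in the control group". The section does not say which test was powered, whether it is one- or two-sided, or on which scale 0.2 is measured.

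The Statistical analysis section describes the comparison that this sample must support. Changes in average daily drinking "before and after intervention are compared with the differences between the two groups". For these and the other comparisons, "we use the *t*-test, paired *t*-test, Wilcoxon rank-sum" and other tests are listed, to be chosen after looking at the distributions. No analysis of variance or covariate-adjusted model is named.

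For one of the two studies cited as the basis of the calculation, the Background reports that "the estimated effect size was small (0.16"), without naming the metric.

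No inflation for dropout is stated. The Monitoring section says that "the recruitment will be suspended when the number of subjects to be analyzed reaches the target", so 200 is taken below as the number analysed.

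**The concern.** The trial compares two independent arms. A reader who sees an effect size of 0.2 next to a planned t-test will take it as a difference of 0.2 standard deviations between arms. For that comparison, 199 in total is about a quarter of the number needed for 80% power (788).

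The power statement governs how a null result is read. If the true difference were 0.2 SD, a two-sided test with 100 per arm would miss it about 71% of the time (1 − 0.29), whereas the stated power implies 20%. A non-significant result could then be taken as evidence that genotype information adds nothing, when the trial could reliably detect only a difference about twice as large.

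**Working it through.** **Inputs.** Effect size 0.2 (metric not stated), alpha 0.05, power 0.8 and 100 per arm, all from the Sample size section. Sidedness is not stated; two-sided is assumed, and one-sided is shown where it matters. Power is computed from the noncentral t or F distribution.

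**Step 1: reproduce 199.**

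*Route A, paired or one-sample t-test.* Noncentrality = dz × √n, with n − 1 degrees of freedom.
- n = 198: 0.2 × √198 = 2.814, power 0.7997.
- n = 199: 0.2 × √199 = 2.821, power 0.8017.

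The smallest n reaching 80% is 199. This powers a before–after change in one group of 199, but neither arm has 199 people and the randomised comparison is not tested.

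*Route B, two-group F-test with Cohen's f.* Noncentrality = f² × N, with 1 and N − 2 degrees of freedom.
- N = 198: 0.04 × 198 = 7.92, power 0.7997.
- N = 199: 0.04 × 199 = 7.96, power 0.8017.
- N = 200: 0.04 × 200 = 8.00, power 0.8036.

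This also crosses 80% at 199. With two equal groups d = 2f, so f = 0.2 means d = 0.4.

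*Other routes at 0.2 do not give 199.*

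| Calculation (80% power) | Total N |
|---|---|
| Two-sample t-test, d = 0.2, two-sided | 788 (394 per arm) |
| Two-sample t-test, d = 0.2, one-sided | 620 (310 per arm) |
| Paired t-test, dz = 0.2, one-sided | 156 |
| Chi-square test, w = 0.2 | 197 |
| Correlation, r = 0.2 | 194 |

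**Step 2: power of the two-arm comparison with 100 per arm.** Noncentrality = d × √(n₁n₂/(n₁ + n₂)) = d × √(100 × 100/200) = d × 7.071, with 198 degrees of freedom and a two-sided critical value of 1.972.

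| d | Noncentrality | Power, two-sided 5% |
|---|---|---|
| 0.20 | 1.414 | 0.291 |
| 0.30 | 2.121 | 0.560 |
| 0.40 | 2.828 | 0.804 |

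One-sided at d = 0.20, power is 0.407. The smallest d with 80% power, two-sided, is 0.398.

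**Step 3: the published effect of 0.16.** Its metric is not given. If it is d, power with 100 per arm is 0.203. If it is f, then d = 2 × 0.16 = 0.32, the noncentrality is 0.32 × 7.071 = 2.263 and power is 0.615. The documents do not allow a choice between about 20% and about 61%.

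**The case against.** The best defence is Route B. A two-group F-test with one numerator degree of freedom is the same test as the two-sided two-sample t-test, so powering through f is compatible with the planned analysis. It gives 199, and rounding up to two equal arms gives 200. On that reading 199, 200 and 80% are all correct for the randomised comparison, and the only defect is a missing label. The odd total does not settle the matter, because both routes cross 80% at 199.

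This stands, and it limits the claim. A reader might infer that the trial certainly has only 29% power at its design effect. The documents do not support that, because they never say that 0.2 is Cohen's d. A reader might also carry over the Background's description of 0.16 as small and treat 0.2 as a conventional small effect; the Sample size section does not call it that. Nor can 0.16 be set against 0.4 as though both were standardised mean differences: its metric is unknown, and it comes from a study of AUDIT scores and risk zones at three months, not grams of alcohol.

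The defence does not make the statement adequate as written. A t-test is normally powered with d or dz, and the article names no F-test. Under Route A the design is the wrong one. Under Route B the sample is adequate only for a difference of 0.4 SD, which the article never says.

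Adjustment for baseline is no clear rescue. If 0.2 is already the standardised difference in change, power remains 29%. If it is on the raw scale, covariate adjustment divides it by √(1 − r²), and 80% power needs r of about 0.87 between baseline and follow-up (0.2/√(1 − 0.865²) = 0.399). Neither such a correlation nor an adjusted model is stated.

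**Conclusion.** The concern holds in conditional form. The stated inputs and the total of 199 fit together only as a paired or one-sample calculation, which is not the randomised comparison, or as a two-group F-test at f = 0.2, which is a difference of 0.4 SD between arms. On the natural reading for a between-arm t-test, d = 0.2, 100 per arm gives about 29% power two-sided (41% one-sided), and 80% would need 394 per arm. What 100 per arm supports at 80% is a difference of about 0.40 SD.

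These figures assume 200 analysed participants, equal arms, a t-test and, unless noted, a two-sided 5% level. Which calculation the authors ran cannot be established from the article, so this is not proof that they used the wrong design. The statement does need correcting, and the same correction is right under either route.

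**What to change.** Keep 200 participants and replace the power statement with, for example:

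> With 100 per arm, a two-sided 5% two-sample comparison has 80% power for a standardised mean difference of about 0.40 (Cohen's f = 0.20) and about 29% power for 0.20.

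Name the test, its sidedness and the effect-size metric. Commit to reporting the between-arm difference in the primary outcome with its 95% confidence interval, and state that a non-significant result will not be read as excluding differences below about 0.4 SD. Give no power figure for the published effect of 0.16 unless its metric is confirmed.

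The cost is wording only: no added participants and no change to conduct. Read as a claim about 0.2 SD, the stated power becomes less favourable.
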